### Assessment of the effects of preleukapheresis IFN-α on DC potency

#### Immunologic potency analysis

The co-stimulatory ability of the vaccine will be assessed with a modified version of the COSTIM assay [48] utilizing IFN-γ as a read-out system which has been used in our laboratory to assess the equivalence of freshly-made *vs* cryopreserved vaccine (data not shown). This GMP-validated method relies on the capacity of co-stimulatory signals provided by DC, *per se* unable to fully activate responder T cells, to trigger a proliferative response or cytokine secretion in allogeneic T cells stimulated with substimulating doses (0.005 mg/ml) of the anti-CD3 antibody OKT3. Briefly, 1×10^5^ reference T cells are co-cultured in quadruplicate with DC in IFN-γ ELISPOT plates for 24 hours at a T:DC ratio of 10:1, in the presence of 0.005 mg/ml OKT3. T cells cultured in the presence of 0.005 mg/ml OKT3 or DC are used as negative control. To ensure intra- and inter-assay reproducibility, reference T cells from at least 3 healthy donors are used for each determination. After a 24-hour incubation at 37°C in 5% CO2, plates are developed according to the manufacturer’s instructions and evaluated by a computer-assisted ELISPOT reader (Eli.Expert, A.EL.VIS GmbH). The distribution of SFC numbers across the different treatment arms (IFN-α *vs* no-IFN-α) will be evaluated according to the Student’s t-test and, if the differences are found to be statistically significant, the specific primary objective will be considered fulfilled. For this endpoint, only the first leukapheresis will be included in the analysis.

#### Assessment of the effects of preleukapheresis IFN-α on TEM-8 expression

We demonstrated in previous works that patients who show upregulation of TEM-8 in DC after maturation (as assessed by flow cytometry and real-time PCR) do not develop anti-tumor immunity after DC vaccination. In order to assess this specific objective, total RNA will be extracted from immature and mature DC (5 × 10^6^ cells) and reverse transcribed to cDNA. Quantitative real-time PCR will be then performed using primer sets that cover all human TEM-8 splicing variants; appropriate housekeeping genes will also be amplified as normalization controls. The ratio between TEM-8 mRNA expression (normalized against housekeeping genes) in monocytes and in mDC will then be calculated. The distribution of the TEM-8 mRNA iDC:mDC ratio observed in the different treatment arms (IFN-α *vs* no-IFN-α) will be then evaluated using the Student’s t-test. If the differences are found to be statistically significant, the specific primary objective will be considered fulfilled.

### Sample size

This is a “randomized selection design” study based on the assumption that immunotherapy is expected to be effective only in patients showing efficient induction of antitumor immune responses (“targeted endpoint”) [49]. The Steinberg and Venzon approach permits the researcher to select one among a number of different treatment arms as being worthy of further evaluation in a subsequent study. This method requires an adequate gap in the number of immune responses among different arms be observed in order to limit the probability that the selected arm is, in actual fact, inferior to the others. Assuming an error probability of selecting an inferior arm of 10%, a gap of 2 patients with an immune response out of a total of 6 enrolled patients per arm is sufficient, regardless of the proportion of irOR expected in each arm, to show that the difference between the highest probability of response and the best response of the remaining arms is 15%. If the gap is inferior to 2 patients, no treatment arm can be considered better than another and new immunostimulating therapies will have to be identified to combine with the DC vaccine.

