### Potential effects of Interferon-α (IFN-α) on circulating precursors of DC

IFN-α is a cytokine belonging to type-I interferons that is currently approved for clinical use in B-cell non-Hodgkin’s lymphoma, advanced renal cell cancer and, in the adjuvant setting, malignant melanoma. This cytokine is secreted by virtually all cells after challenge with viral or bacterial products, but it can also be produced by transformed cells or by normal cells under mitogenic stimulus. Its effects on tumor or virus-infected cells are pleiotropic, ranging from the direct inhibition of proliferation to the suppression of oncogene expression and the induction of tumor suppressor genes. Moreover, IFN-α positively affects the activity of both the adaptive and innate immune system, and enhances immune recognition of tumor cells [24]. Furthermore, IFN-α inhibits the expression of the proangiogenic inflammatory cytokine, interleukin-8 (IL-8), and IL-1β [25], both of which induce an immunosuppressive phenotype in monocyte-derived DC [23].

It is tempting to speculate that treatment with IFN-α, whilst inhibiting the expression of IL-1β, may also suppress the maturation-induced TEM-8 upregulation of DC observed in non-immunoresponsive patients, thus revertingthe TEM-8 associated immunosuppressive phenotype. In partial support of this hypothesis is our observation of positive immunization to DTH in all patients who underwent therapy with IFN-α a maximum of 30 days before starting DC vaccination (our unpublished data), suggesting that IFN-α priming performed *in vivo* before leukapheresis may enhance the immunostimulatory profile of DC. Moreover, IFN-α priming may also have a “mobilizing” activity on DC precursors: it was recently reported that 1–3 MU subcutaneous IFN-α enhances the proportion of circulating CD14+ and CD14 + CD16+ monocytes in both healthy donors and melanoma patients [26].

In the light of these findings, administration of IFN-α before leukapheresis may positively modulate the immunological and clinical efficacy of DC vaccination.

In particular, preemptive IFN-α should:

– (1.) lead to the production of more highly immunogenic monocyte-derived DC;

– (2.) mobilize peripheral DC precursors, thus enhancing leukapheresis yields;

– (3.) positively modulate the immunogenicity of melanoma cells *in vivo*.

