Randomization guarantees the avoidance of selection bias, excluding the preferential inclusion of patients in certain treatment arms. This approach, whilst not identifying which factors contribute to immunogenicity or which regimens are significantly better than others, will, however, highlight a treatment or treatment combination that warrants further investigation. The sample size per treatment must be large enough to ensure, with strong probability, that if one treatment or treatment combination is superior to all others by a specific amount, then it will have the largest sample mean and will therefore be selected. In particular, if one of the external immunostimulant conditions investigated shows higher clinical activity than that observed in the other conditions by a predetermined amount, that condition will be superior to the others with a given probability and will merit further clinical investigation. By enrolling six patients in each treatment arm, we will obtain a 90% probability of correctly selecting the best investigated external immunostimulant condition if the superior arm, if present, has a true expected outcome that is at least 15% higher in terms of irDCR (immune-related disease control rate) than that of the inferior arms [46]. Otherwise, the immunological primary endpoint (immunological efficacy) will guide the choice of treatment combination to further develop using the same method. If a treatment or a combination of treatments is not identified as superior, the vaccine regimen (without external immunostimulant conditions) will be considered for further investigation.

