#### Leukapheresis and vaccine manufacturing

At the end of the screening phase, patients will be randomized and will enter the leukapheresis and vaccine manufacturing phase. Each patient will be assigned to one of the following arms:

(1.) three daily doses of 8 Gy - 12 Gy radiotherapy delivered to one non-index metastatic field (optional to one additional field) between vaccine doses 1 and 2 and between doses 7 and 8, using IMRT-IMAT techniques;

(2.) daily 3 MU subcutaneous IFN-α for 7 days before leukapheresis;

(3.) both 1 and 2 external immunostimulant conditions;

(4.) neither 1 nor 2 external immunostimulant conditions.

At least six patients eligible for treatment will be enrolled per arm.

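### A lead of fewer than 2 of 6 responders is taken as grounds to look for new stimulants, although two arms sharing a working stimulant will usually finish within 2 of each other

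*Protocol article*

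**What the plan says.** The trial has four arms in a 2×2 layout: RT (arm 1), IFN-α (arm 2), "both 1 and 2 external immunostimulant conditions" (arm 3) and neither (arm 4), with at least six patients in each.

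The Sample size section sets the selection rule: "a gap of 2 patients with an immune response out of a total of 6 enrolled patients per arm is sufficient". The comparison is between the top arm and the best of all the others: "the difference between the highest probability of response and the best response of the remaining arms is 15" per cent. The error behind it is stated as "Assuming an error probability of selecting an inferior arm of 10" per cent. For a smaller lead the section says: "If the gap is inferior to 2 patients, no treatment arm can be considered better than another and new immunostimulating therapies" will be needed.

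Trial design and statistical considerations gives another outcome for the same event: "If a treatment or a combination of treatments is not identified as superior, the vaccine regimen (without external immunostimulant conditions) will be considered" for further study. That section selects first on irDCR. If that does not decide, it turns to the immunological endpoint by the same method.

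**The concern.** Two separate things are wrong with the consequence attached to a small lead.

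First, the 10% limits the chance of picking a worse arm. It says nothing about how often the rule fails to pick a good one, so it cannot support a negative conclusion about the stimulants.

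Second, the rule measures each arm against every other arm, including the one that shares its stimulant. If IFN-α works to a similar degree with and without RT, arms 2 and 3 rise together and compete with each other for the lead. The more alike their benefit, the less likely it is that either leads by 2. The same holds for RT in arms 1 and 3.

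What is at stake is which regimen is developed next. Under either section's no-winner outcome both stimulants are set aside, on a result that a working stimulant would commonly produce.

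**Working it through.** **Inputs from the protocol.** 6 patients per arm; required lead of 2; 15-point difference; 10% error (Sample size). Vaccine-alone immune response about two-thirds (Dendritic cell vaccination). Vaccine-alone clinical benefit 55.5% (same section).

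**Assumptions.** Patients are independent and response is binary. IFN-α works equally in arms 2 and 3, and RT has no effect. The 30% baseline and all effects other than 15 points are chosen to show a range.

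**Method.** Responders in arm i are X_i ~ Bin(6, p_i), so P(X_i = x) = C(6,x) p_i^x (1−p_i)^(6−x). An arm is selected only if the largest count exceeds the second largest by at least 2. P(no arm selected) is the sum of the products of the four probabilities over all 7⁴ = 2,401 outcomes in which the lead is 0 or 1.

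**The plan's own figure.** With three arms at p and one at p + 0.15, the chance of selecting one of the three inferior arms, maximised over p, is 8.6% at a lead of 2. At a lead of 1 it is 31.9%. The stated 10% bound with a lead of 2 therefore reproduces. It is a bound on wrong selection only.

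**Why a tie is expected.** At two-thirds plus 15 points, expected counts are 6 × 0.667 = 4.0 without IFN-α and 6 × 0.817 = 4.9 with it. The expected difference between the two IFN-α arms is 0.

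**P(no arm selected):**

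| Without v with IFN-α | IFN-α works in arms 2 and 3 | No effect, all arms at baseline |
|---|---|---|
| 67% v 82% (+15 points) | 91% | 87% |
| 67% v 90% | 95% | 87% |
| 55.5% v 70.5% (+15 points) | 83% | 82% |
| 55.5% v 85.5% (+30 points) | 87% | 82% |
| 30% v 60% (+30 points) | 71% | 81% |

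**Chance that an IFN-α arm is the one selected.** At 67% v 82% each IFN-α arm is picked in 4.1% of trials, so 2 × 4.1 = 8.2%. With no effect it is 2 × (100 − 86.8)/4 = 6.6%. At 55.5% v 70.5% it is 2 × 7.2 = 14.4%, against 2 × (100 − 82.3)/4 = 8.9%.

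**When one arm stands apart.** If the combination is clearly best, at assumed rates of 45% (RT), 45% (IFN-α), 90% (both) and 30% (neither), arm 3 is selected in 65% of trials. At 50/50/80/30% it is 39%. At a 55.5% baseline with additive 15-point effects it is 12%.

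**Whether other text repairs this.** The fallback to the immunological endpoint uses the same method, so it meets the same tie. IFN-α v no-IFN-α comparisons are planned for DC yield, potency and TEM-8, not for immune response or irDCR.

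**The case against.** The strongest defence is that this is an exploratory selection design meant to pick one regimen of four, and that it does what it promises: wrong selection stays within 10%. The Trial design section itself disclaims identifying which factors contribute. If the two stimulants act together strongly, the rule can find the combination. DTH scores and ELISPOT results are also compared across arms and could show two raised arms. All of this stands. It does not rescue the consequence, because those comparisons do not feed the selection rule, and a design that disclaims factor conclusions should not require new stimulants after a small lead.

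Some stronger readings are tempting, and the protocol does not support them:

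- A reader might infer that the plan claims proof of equality. It says only that no arm can be considered better; the fault lies in the action that follows.
- A reader might infer that the rule always does worse when a stimulant works. At 30% v 60% non-selection is 71%, below the 81% with no effect.
- A reader might infer that losing IFN-α is certain, since the protocol reports "positive immunization to DTH in all patients who underwent therapy with IFN-α a maximum of 30 days before starting DC vaccination". Setting response at 100% in arms 2 and 3 does give no selection in 100% of trials, but that rests on unpublished data with no sample size given, and makes the tie certain by construction.
- A reader might infer that vaccine alone has no role in the decision. The Trial design section makes it the default when nothing is superior.

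**Conclusion.** The point holds and is moderate in weight. A lead under 2 of 6 is an inconclusive result, and the Sample size section acts on it as if it counted against the stimulants. At the protocol's baselines of 55.5% and two-thirds, no arm is selected in 83% to 95% of trials when IFN-α works in both its arms by 15 points or more (up to 30 points at 55.5%, up to 90% response at two-thirds). With no effect the figures are 82% and 87%. Failure to select is therefore close to uninformative about a shared stimulant there.

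This rests on a roughly equal effect in both arms and an inert second stimulant. It weakens at lower baselines and where the combination is far ahead. Separately, and without any calculation, the two sections prescribe different next steps when there is no winner: new stimulants in one, vaccine without stimulants in the other. The trial's exploratory purpose and the fact that the consequence concerns later development keep this below a must-fix.

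**What to change.** 1. In Sample size, replace the consequence of a lead under 2 with: *no single arm is selected; the result is inconclusive and is not evidence that the regimens are equal or that a stimulant is ineffective.* Delete the automatic need to identify new stimulants.
2. Report, as descriptive results with exact confidence intervals, each stimulant arm's difference in response from vaccine alone (6 v 6), and the IFN-α v no-IFN-α and RT v no-RT differences (12 v 12 at minimum enrolment).
3. Reconcile the no-winner outcome in Trial design and statistical considerations with the one in Sample size, so that one event has one stated consequence.

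The cost is wording and a small table, with no extra patients or procedures. The no-winner statement becomes less definite, and the intervals will be wide at these sizes. A formal rule for carrying a shared stimulant forward is not required: one that demands both arms with the stimulant lead both arms without it by 2 would fire in only 8% to 9% of trials at a 15-point effect.

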## Discussion

The recent development of targeted agents and new drugs has partially changed the clinical course of advanced melanoma patients. Toxicities from BRAF inhibitors or anti-CTLA-4 antibodies for melanoma, albeit low grade, are continuous and chronically impact on quality of life. Furthermore, some toxicities with an initially mild presentation can progress, if not rapidly recognized, into severe and potentially life-threatening events [50,51]. Conversely, the use of vaccines in melanoma patients has been historically associated with negligible toxicity, although clinical results are disappointing and somewhat contrasting. However, encouraging results have been reported in several studies of vaccination with dendritic cells, albeit obtained on small series of patients.

In this context we recently reported the results from a phase II clinical study of DC-based vaccine in metastatic melanoma in which 55.5% of evaluable patients showed a clinical benefit (PR + SD), with very low toxicity [15,16]. Like us [16,18], other groups [17] also observed that, patients who developed anti-tumor immunity after vaccination experienced a better clinical outcome. In particular, we saw that individuals developing delayed type hypersensitivity (DTH) against autologous tumor lysate or KLH after at least four courses of the vaccine showed a median OS of 22.9 months compared to 4.8 months for DTH-negative cases (Log-rank test, p = 0.007) [16].

These results prompted us to use combination treatments aimed at improving the rate of patients showing positive immunization after vaccination. In particular, we observed that all those who underwent therapy with low-dose IFN-α in the month before starting DC vaccination (unpublished data) showed positive immunisation after the first induction doses, suggesting that IFN-α priming, performed *in vivo* before leukapheresis, may enhance the immunostimulatory profile of DC. Moreover, IFN-α priming may also have a “mobilizing” activity on DC precursors: it was recently been reported that 1–3 MU subcutaneous IFN-α enhances the proportion of circulating CD14+ and CD14 + CD16+ monocytes in both healthy donors and melanoma patients [26]. On this basis, the administration of IFN-α before leukapheresis may positively modulate the immunological and clinical efficacy of DC vaccination. In addition to the potential for preleukapheresis IFN-α to improve the immunological efficacy of monocyte-derived DC vaccine, a synergism between immunotherapy and radiotherapy (the abscopal effect) has hypothesized in which radiotherapy “immunizes” the patient against cancer cells, converting the irradiated tissue into an *in situ vaccine*. Although, in some cases, radiotherapy alone can induce immunological memory protection, in others it loses its initial efficacy when recurrence occurs. Overall, findings from the literature suggest that radiotherapy may also act as an “immune response modifier” which can correct the immunosuppressive network created by tumor cells. In that respect, radiotherapy would seem to be capable of recovering the cancer-specific immune response after failure of immunotherapy, of boosting the naturally occurring anti-tumor immune response, and cooperating with cancer vaccines to facilitate the priming of a non-immunodominant response [52,53].

We designed a randomized, proof-of-principal study in which preleukapheresis radiotherapy and/or IFN-α are added to the DC vaccine with the aim of enhancing the vaccine-induced tumor immune response and, in doing so, of potentially improving survival. Moreover, these combination therapies should, in theory, maintain the same low toxicity profile observed in our previous studies. Dose and fraction of radiotherapy and the correct sequencing of therapies will also be evaluated. The identification of an effective treatment regimen could be used in a phase III trial or be applied to clinical practice.

## Abbreviations

AE: Adverse event; ALT: Alanine aminotransferase; ANC: Absolute neutrophil count; ASAT: Aspartate aminotransferase; AR: Adverse reaction; ATL: Autologous tumor lysate; CBC: Complete blood count; CI: Confidence interval; CNS: Central nervous system; CTLA-4: Cytotoxic T-lymphocyte antigen 4; CTscan: Computed tomography; CTC: Common toxicity criteria; DC: Dendritic cells; DCR: Disease control rate; DFS: Disease free survival; DM: Ministerial Decree; DTH: Delayed type hypersensitivity; ECOG: (Eastern Cooperative Oncology Group, ECOG Scale) Performance status; GCP: Good Clinical Practice; GM-CSF: Granulocyte/Monocyte colony stimulating factor; GMP: Good Manifacturing Practice; iDC: immature dendritic cells; IFN-α: Interferon α; Il-1β: Interleukin-1β; IL2: Interleukin 2; IL4: Interleukin 4; IL6: Interleukin 6; IL8: Interleukin 8; IR: Ionizing radiations; irBOR: immune-related best overall response; irCR: immune-related complete response; irDCR: immune-related disease control rate; irDOR: immune-related duration of response; irORR: immune-related overall response rate; irPD: immune-related progressive disease; irPFS: immune-related progression-free survival; irPR: immune-related partial response; irRC: immuno-related response criteria; irSD: immune-related stable disease; irTTP: immune-related time to progression; irTTR: immune-related time to response; KLH: Keyhole lympet hemocyanin; MHC: Major histocompatibility complex; NK: Natural killer; OS: Overall survival; PGE2: prostaglandin E2; PD: Progressive disease; RECIST: Response Evaluation Criteria In Solid Tumors; RT: Ionizing radiation therapy; SD: Stable disease; SFC: Spot forming cells; SPD: Sum of the perpendicular diameters; TEM-8: Tumor endothelial marker-8; TNF-α: Tumor necrosis factor α; TPFS: Total progression-free survival; irTTP: Immune-related time to progression; WBC: White blood cells; WHO: World Health Organization.
